#### Inspiratory muscle function

Inspiratory muscle function will be determined measuring the maximum static inspiratory pressure that the patient can generate at the mouth (i.e., PI_max_) against an occluded system (i.e., Müller’s maneuver) (Micro Medical/CareFusion, Kent, UK) [80, 81]. Properly seated, patients will be instructed to exhale up to their residual volume and will be then encouraged to inspire as fast and strong as possible for 3 seconds. The highest 1-second average value will be recorded in each trial. The best three reliable measurements (i.e., < 10% coefficient of variation) will be obtained from a range of 5 to 8 maximum trials separated by 60 seconds of rest.

#### Anxiety and depression

The degree of anxiety and depression will be determined according to the Hospital Anxiety and Depression Scale (HADS)[82]. This is a questionnaire that includes 14 items in two subscales: 7 items to assess anxiety and another 7 to assess depression. Each item can be scored from 0 to 3 points, so the possible total scores range between 0 and 21 for each subscale. A total score from 0 to 7 implies the absence of anxiety and/or depression, from 8 to 10 suggests the presence of a disorder, and a score of more than 11 indicates a probable presence of a mood disorder [83].

#### Ambulation ability

Ambulatory capacity will be measured with the Functional Ambulation Classification (FAC) scale [84]. This scale assesses the patients’ walking ability on 6 levels according to whether they: cannot walk (level 0); walk with continuous manual contact from one person to maintain balance or to assist coordination (level 1); require light physical contact from a person (level 2); walk alone but require supervision of one person either for safety or verbal cueing (level 3); walk independently on level surface, but cannot negotiate stairs, inclines or non-level surfaces (level 4); or walk independently, including stairs (level 5).

#### Surgical complications

Surgical complications during hospital stay will be objectively classified according to the Clavien-Dindo scale [85]. Different categories (from I to V) are defined on this scale based on the severity of the treatments required by patients after undergoing surgery. Thus, categories I-II are considered as mild and III-V as serious.

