**Methods:**

This randomized, controlled, observer-blinded, single-center trial aims to randomize 250 patients (>74 years) to either an intervention or a control group (i.e., usual care). The intervention group will perform an individualized home-based multicomponent exercise program with weekly telephone supervision from diagnosis until three months post-surgery. The primary outcomes will be HRQoL (EORTC QLQ-C30; CR29; and ELD14**)** and functional capacity (Barthel Index and Short Physical Performance Battery), which will be assessed at diagnosis, at discharge, and one, three, and six months after surgery. Secondary outcomes will be frailty, physical fitness, physical activity, inspiratory muscle function, sarcopenia and cachexia, anxiety and depression, ambulation ability, surgical complications, and hospital length of stay, readmission and mortality.

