The regular practice of physical activity (PA) in cancer patients has been associated with a better HRQoL [18–23], physical function [21, 24] and functional capacity [18]. PA also contributes to reduce mortality risk [25, 26] and muscle atrophy [27, 28]. In this sense, the World Health Organization [29] and the American Cancer Society [30] recommend performing at least 150-300 minutes per week of moderate-intensity PA or 75-150 minutes per week of vigorous-intensity PA (or a combination thereof) involving resistance and endurance exercise – as well as minimizing sedentary behaviors – for primary and tertiary cancer prevention in adults. Moreover, the benefits of physical exercise as an intervention for promoting healthy ageing and treating age-related disorders in older patients with cancer are well documented [20, 21]. However, there is high inter-individual variability on the effects of exercise interventions that can be explained by several factors such as type of cancer, participants’ or interventions’ characteristics, or type of study. Studies on exercise effects in elderly patients with CRC are scarce and methodologically heterogeneous. A recent review [5] which included 11 randomized controlled trials (RCT) concluded that exercise interventions improve functional capacity [31–33] and reduce postoperative complications [34, 35] and length of hospital stay (LOS) [35, 36] in CRC patients with surgical indication over the age of 60 years. Only two RCTs assessed mortality, but no decrease was found in 30-day [36] or 1-year mortality [35] after the intervention. No differences regarding HRQoL were found [32, 37]. However, there is a lack of consensus regarding the most effective exercise type [38], the optimal dose of exercise [39] or the best moment to implement the exercise intervention (prehabilitation vs. rehabilitation) [40, 41]. In this regard, the combination of exercise with other interventions such as nutritional or mental support and behavior modification before surgery (i.e., multimodal prehabilitation) may not provide additional benefits to multimodal rehabilitation, as showed in a recent Cochrane Review [41]. However, the authors concluded that the low number of included participants and studies (only 250 patients among three RCTs) summed to their methodological heterogeneity might have limited the certainty of their conclusions so more and larger studies are needed to gather evidence. On the other hand, adherence to these programs is often inconsistently reported, and there are no clear recommendations on how to increase it [42]. Previous studies have shown that enrollment in exercise trials and adherence to exercise is negatively associated with older age [43, 44]. Some commonly reported barriers include physical symptoms related to cancer or its treatment (e.g. fatigue, peripheral neuropathy, comorbid health conditions, impaired mobility), psychological impact of cancer diagnosis, many hospital appointments, lack of information, lack of social support, and other constrains regarding time, costs, access and guidance [44, 45]. Low-cost and easily accessible programs that can be carried out at home and that are supported and guided by professionals (via direct supervision, written materials or by phone) may improve adherence to exercise [44, 46]. Therefore, the design of these programs should be adapted according to the characteristics of the population studied, the patient’s individual level of performance, the proposed outcomes and patient’s preferences [5, 47].

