
There is still a lack of knowledge on the benefits of exercise in older and more vulnerable patients, who are precisely those with the highest risk of complications and the greater loss of functional independence and HRQoL after CRC treatment. For this reason, we aim to study the effects of an individualized home-based multicomponent exercise program, supervised by a clinical exercise physiologist through telephone calls, on functional capacity and HRQoL in older adults undergoing elective CRC surgery when compared to usual care. Our primary hypothesis is that the exercise program improves functional capacity and HRQoL of older patients with CRC compared to usual care. The secondary aims will be to investigate the effect of the exercise program on physical performance, surgical complications and hospital readmissions, the prevalence of frailty, anxiety and depression, sarcopenia and cancer-cachexia, as well as the effects on physical fitness and inspiratory muscle function in comparison to usual care. Furthermore, the intervention’s safety and feasibility will be studied by registering patient’s adverse events and adherence to the program.

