### Randomization and blinding

Patients who fulfill the inclusion criteria and accept to participate will be randomly assigned (1:1) to an intervention (IG) or control group (CG) following a computer-generated (Sealed Envelope Ltd. 2021) allocation sequence using a fixed block size of 6. The allocation sequence and resulting patient assignment will be concealed from study members involved in participants’ enrollment and assessment. Patients will be notified about allocation consignment by the study member involved in the intervention delivery, who will advise to participants not to discuss about their treatment assignment with blinded staff. Participants and care providers will be not blinded to the treatment group. By contrast, data collection and analysis will be performed by researchers blinded to the group allocation of the patients.

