#### Hospital length of stay, readmissions, and mortality

The LOS associated to CRC surgery will be computed as the number of days from hospital admission for surgery to discharge. The number of hospital readmissions, the length of stay of these readmissions as well as the incidence of all-cause mortality will be registered thought the study.

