## Discussion

This study aims to determine whether an individualized home-based exercise program supervised by telephone improves or maintains HRQoL and functional capacity in patients ≥ 75 years old during CRC treatment when compared with usual care.

Our main hypothesis is that this individualized home-based exercise program supervised by telephone will improve the HRQoL and functional capacity of older adults following CRC treatment. Although exercise interventions are highly recommended as they provide numerous benefits to people affected by cancer in general, studies including very old populations (i.e., aged 75 years and over) are practically null. Several RCTs on CRC patients aged over 60 years have reported that regular PA improves functional capacity [31–33], reduces postoperative complications [34, 35] and LOS [35, 36]. In contrast, other studies have reported no reduction of 30-day [36] or 1-year mortality [35], nor improvements in HRQoL [32, 37].

As recommended by international guidelines for primary and tertiary cancer prevention in adults [30, 92, 93], most studies include a combination of strength and endurance training. Moreover, most studies include supervised training sessions performed in hospitals or sport centers. Considering that our patients are very old, and adherence is reduced with older age, the inclusion of home-based exercise sessions supervised weekly by phone calls may be an alternative, particularly when accessibility issues, lack of mobility or time constraints are barriers to participate. Nevertheless, scarce information exists regarding the most effective way of training and how to improve adherence to the exercise program for promoting healthy ageing and treating age-related disorders in older people during and after CRC.

To the best of our knowledge, this will be the first RCT conducted in a very old population (over 74 years) of CRC patients, who indeed present more physical, mental, social and emotional limitations and who have an increased risk of suffering the negative consequences of surgery compared with younger populations. Another novelty of our study is that our exercise program will also include inspiratory muscle training unlike other multicomponent programs.

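### Clavien-Dindo complications are counted only up to discharge, so if exercise shortens the stay the comparison can favour exercise with no true difference

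*Protocol article*

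**What the plan says.** The section on surgical complications sets the outcome and its window in one sentence: "Surgical complications during hospital stay will be objectively classified according to the Clavien-Dindo scale". It gives no fixed number of days after the operation. The section on length of stay fixes where the window ends, because the stay is "computed as the number of days from hospital admission for surgery to discharge".

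The abstract lists both among the secondary outcomes: "surgical complications, and hospital length of stay, readmission and mortality". The last paragraph of the Background makes the effect of exercise on "physical performance, surgical complications and hospital readmissions" a secondary aim, so complications will be compared between arms.

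On the direction to expect for length of stay, the Background says of earlier trials that exercise interventions "reduce postoperative complications [34, 35] and length of hospital stay (LOS"), and the Discussion repeats that activity "reduces postoperative complications [34, 35] and LOS [35, 36"].

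Data are also collected after discharge. Readmissions, their length and all-cause deaths are registered throughout the study. Medical staff record adverse events under CTCAE version 5.0 for the study duration. Visits follow at 1, 3 and 6 months. No text shown brings these data into the Clavien-Dindo outcome.

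**The concern.** A count of events is comparable between arms only if the time over which events are counted is the same, or at least does not depend on treatment. Here the time ends at discharge, and discharge is something the trial itself treats as a possible effect of exercise. If patients in the exercise arm go home sooner, a complication that would have begun on the ward in the control arm begins at home and is not counted.

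Analysis by intention to treat does not repair this, because the fault lies in the outcome definition and not in who is analysed. What is at stake is a stated secondary aim: a report of fewer surgical complications that partly reflects a shorter counting window.

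**Working it through.** **The plan's own figure.** There is none for this outcome. The protocol article states no complication rate, no onset times, no expected stay and no power for it. What follows illustrates the mechanism and does not estimate it.

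**Inputs from the protocol article.** 125 patients per group (section on sample size) and a significance level of 0.05 (section on statistical analysis), taken as two-sided as in the sample-size section.

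**Inputs assumed, not in the documents.**
- True 30-day complication risk p, equal in both arms: 30%, 40% or 50%.
- Onset after surgery declining exponentially with scale m: 4, 6 or 10 days.
- Day of discharge L, control vs exercise: 8 vs 7, 8 vs 6 or 10 vs 7.

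**Formula.** The rate counted in hospital is

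R(L) = p × (1 − exp(−L/m)) / (1 − exp(−30/m)).

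**Worked case, p = 40%, m = 6, stays of 8 vs 6 days.**
- Denominator: 1 − exp(−5) = 0.9933.
- Control: 0.40 × (1 − exp(−8/6)) / 0.9933 = 0.40 × 0.7364 / 0.9933 = 29.7%.
- Exercise: 0.40 × (1 − exp(−6/6)) / 0.9933 = 0.40 × 0.6321 / 0.9933 = 25.5%.
- Apparent difference 4.2 points and risk ratio 0.86, with no true effect.
- Chance of a significant result favouring exercise at 125 per arm (normal approximation for two proportions): about 11%, against a nominal 2.5%.

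**Range over all assumed values of p and m.**

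| Stay, control vs exercise | Difference (points) | Apparent risk ratio | Chance of a false result favouring exercise |
|---|---|---|---|
| 8 vs 7 days | 1.2 to 2.5 | 0.91 to 0.96 | 4% to 6% |
| 8 vs 6 days | 2.6 to 5.2 | 0.82 to 0.90 | 7% to 15% |
| 10 vs 7 days | 2.8 to 6.8 | 0.80 to 0.90 | 7% to 21% |

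Letting the stay vary between patients (gamma distribution, shape 6, same means) gives much the same: differences of 1.1 to 6.2 points, risk ratios of 0.80 to 0.96, and a chance of 4% to 19%.

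**Admission before surgery.** The stay is counted from admission, while risk starts at surgery. If admission is one day earlier, stays of 8 vs 6 days leave 7 vs 5 days at risk. In the worked case the rates are then 0.40 × 0.6886 / 0.9933 = 27.7% and 0.40 × 0.5654 / 0.9933 = 22.8%, a risk ratio of 0.82. The simplification changes the size but does not create the effect.

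**With a fixed window.** Counting to day 30 in both arms gives R = p in each, so the expected risk ratio is 1.00 and the chance of a false result favouring exercise returns to about 2.5%.

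**The case against.** **The bias is conditional.** A reader might infer that the planned comparison is biased in favour of exercise. The documents do not show that. Bias arises only if exercise advances the discharge of patients who have not yet had a complication. The same earlier study (reference 35) is cited for both fewer complications and shorter stays. That fits stays being shorter because complications were fewer, and in that case in-hospital counting is not distorted by the stay. Both arms also receive enhanced-recovery care. This objection stands, and the point is stated conditionally for that reason.

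**Unblinded discharge.** The article says "Participants and care providers will be not blinded to the treatment group", and a reader might infer that staff will send exercise patients home earlier. The documents do not say who decides discharge, so this cannot be claimed.

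**Lost events.** A reader might also infer that complications after discharge go unrecorded. They do not: adverse events, readmissions and deaths are collected, and CTCAE is itself a grading system. A reader of the results could see earlier discharge offset by readmissions. What is absent is their Clavien-Dindo grading and their place in this outcome. The data collection schedule (Table 2) is not shown, so later recording of complications cannot be excluded.

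**Size.** Every input to the illustration apart from the group size and the significance level is assumed. A difference in mean stay is not the same as a difference in the discharge day of uncomplicated patients, because complications lengthen the stay. The 4.2-point gap in the worked case is smaller than its standard error: √(0.297 × 0.703/125 + 0.255 × 0.745/125) = 5.6 points. This stands as a limit on size. It does not bring back events that begin after discharge.

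**Unequal detection under a longer window.** Weekly calls are described only within the exercise programme, and exercise-related events such as herniation or stoma leakage are captured on those calls. Adding them to the outcome could bias it against exercise. This stands and shapes the fix.

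**Conclusion.** The point holds in conditional form. The protocol article expressly ends the complication window at discharge, and the cited evidence gives reason to expect that exercise shortens the stay. If it does so by bringing discharge forward, the comparison can favour exercise with no true difference.

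The size cannot be fixed from the documents. Under the assumed inputs the risk ratio runs from about 0.80 to 0.96, and the effect is small if the stays differ by only one day. None of these values should be read as a prediction for this trial.

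The in-hospital definition is clear and contradicts nothing else in the article. This is a design choice worth improving, not an error. It concerns one secondary outcome, and the primary outcomes and the sample size are untouched.

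**What to change.** Define the outcome as complications graded by Clavien-Dindo from the date of surgery to a fixed day that is the same in both arms (for example day 30), regardless of discharge. Keep the in-hospital count as descriptive.

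- **Sources.** Take events after discharge only from sources common to both arms: medical-staff adverse-event records, readmission and mortality records, and the 1-month visit. Do not use the exercise physiologist's weekly calls.
- **Anchor.** State that the window runs from surgery. The section on data collection dates follow-up from discharge, while the abstract and the section on statistical analysis date it from surgery.

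The cost is a change to the outcome definition and some regrading of events after discharge, with no new visit. The drawback is slightly less complete capture of mild events once patients are home.

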#### Hospital length of stay, readmissions, and mortality

The LOS associated to CRC surgery will be computed as the number of days from hospital admission for surgery to discharge. The number of hospital readmissions, the length of stay of these readmissions as well as the incidence of all-cause mortality will be registered thought the study.

#### Other variables

Other variables will be collected through a standard questionnaire administered by duly trained personnel. Include: sociodemographic data, clinical variables, medications, comorbidities [86], characteristics of cancer, American Society of Anesthesiologists (ASA) physical status classification to help predict operative risk [87], type of surgery, adjuvant treatment, presence of geriatric syndromes and medical complications.

### Adverse events and patient-reported outcomes

Patients’ adverse events will be registered during the study duration by the medical staff according to the NCI- Common Terminology Criteria for Adverse Events (CTCAEv5.0). In addition, patient-reported outcomes on cancer treatment derived symptomatic toxicities will be collected weekly through a custom-built survey designed at PRO-CTCAE ^®^ Measurement System (https://healthcaredelivery.cancer.gov/pro-ctcae/). The exercise-related adverse events (i.e., those deemed to be caused by exercise) will be captured by the clinical exercise physiologist during weekly phone monitoring. Exercise-related adverse events will be categorized as musculoskeletal/connective tissue (e.g., delayed onset muscle soreness, strains, joint pain), accidents/injuries (e.g., falls, sprain, tripping), cardiovascular symptoms/conditions (e.g., lightheadedness, dizziness, fainting, and heart palpitations), surgery-related (e.g., herniation, stoma leakage, scar tissue pain) or others, as proposed elsewhere [88].

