## Interventions

### Control group (CG)

Participants randomly assigned to the control group will receive the usual care, which includes the Enhanced Recovery for Abdominal Surgery (ERAS) by the surgery department [49, 50]. This includes oral and written information on diet, avoiding sedentary lifestyle and breathing exercises with a spirometer, among other items that try to assure an early post-operative recovery. The participation of the geriatric team includes the CGA-guided intervention, mostly focused on the management of frailty and other geriatric syndromes, such as malnutrition, functional impairment, cognitive decline or depression and quality of life. In addition, the clinical exercise physiologist will give participants general advice about the positive effects of PA and will encourage them to reduce sedentary lifestyle.

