#### Adherence and exercise monitoring

Patients will be contacted weekly on a 20-minute telephone support session by the clinical exercise physiologist to report adherence to the home-based training. Thus, every week they will receive an explanation about the purpose of the intervention and the possible benefits of the exercises and progress will be reviewed. Motivation strategies will be used for achieving engagement to sustain exercise activity and/or achieve higher or progressively more intense performance. These strategies are based on the principles of Self Determination Theory [58]. Participants will have the opportunity to discuss any issues related to their exercise program and any barriers to exercise will be taking into consideration. Attendance of each participant will be recorded and reasons for dropouts will be documented.

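### Exercise-related adverse events are elicited weekly in the intervention arm only, by the unblinded programme deliverer, so event types that also occur in controls are ascertained unequally

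*Protocol article*

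**What the plan says.** The section on adverse events and patient-reported outcomes sets out three routes.

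1. Medical staff: "adverse events will be registered during the study duration by the medical staff according to the NCI- Common Terminology Criteria for Adverse Events (CTCAEv5.0". No arm is singled out.
2. A patient survey: "patient-reported outcomes on cancer treatment derived symptomatic toxicities will be collected weekly through a custom-built survey". Again no arm is singled out, but the subject is toxicity of cancer treatment.
3. The physiologist: "The exercise-related adverse events (i.e., those deemed to be caused by exercise) will be captured by the clinical exercise physiologist during weekly phone monitoring". The categories for this third route include "accidents/injuries (e.g., falls, sprain, tripping), cardiovascular symptoms/conditions (e.g., lightheadedness, dizziness, fainting, and heart palpitations), surgery-related (e.g., herniation, stoma leakage, scar tissue pain", besides musculoskeletal complaints.

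The weekly call is part of the intervention. The abstract states: "The intervention group will perform an individualized home-based multicomponent exercise program with weekly telephone supervision from diagnosis until three months post-surgery". The section on adherence and exercise monitoring gives its purpose: "Patients will be contacted weekly on a 20-minute telephone support session by the clinical exercise physiologist to report adherence to the home-based training". For controls, the article says that "the clinical exercise physiologist will give participants general advice about the positive effects of PA" and encourages them to be less sedentary. It describes no call to them.

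Safety is a stated aim. The Background says that "safety and feasibility will be studied by registering" adverse events and adherence. The section on randomization and blinding says that care providers know the allocation, while data collection is done by blinded researchers.

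**The concern.** Most of the listed event types are not specific to exercise. The article itself labels herniation, stoma leakage and scar pain as surgery-related, and both arms have surgery. Its section on physical performance links low SPPB scores to a high risk of falls, which applies to either arm. A control patient who stumbles at home or feels dizzy has had the same kind of event as an exercising patient, but only the latter is telephoned every week by someone whose task includes recording it.

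Whoever hears of the event also matters. It enters this category only if it is deemed caused by exercise. The article names no judge of that other than the physiologist, who prescribes and supervises the exercise. For this outcome the collector is not blinded, despite the general statement on blinded data collection.

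At stake is how the safety aim can be answered. The article does not say whether an event learned in a call also enters the CTCAE register. If it does, the exercise arm can look less safe with identical true rates. If it does not, the exercise-related figure is a single-arm count whose attribution rests with the deliverer.

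**Working it through.** The plan gives no event rate, detection rate or safety comparison to reproduce, so the main check sets the routes side by side.

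| Route | Arms | Who | Elicitation stated | Covers falls, sprains, hernias at home? |
|---|---|---|---|---|
| CTCAE register | both | medical staff | study duration, no interval given | yes, if reported to staff |
| PRO-CTCAE survey | not limited | patient | weekly | not by its wording; may overlap on symptoms such as dizziness |
| Exercise-related events | intervention, as described | physiologist | weekly call | yes, named as categories |
| Clavien-Dindo | both | not stated | hospital stay only | no |
| Readmissions, mortality | both | not stated | throughout | only if serious |

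For minor events at home, the weekly call is the one route that combines active elicitation with these categories, and it is described for one arm.

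**Number of contacts.** The post-operative programme lasts 12 weeks. If the wait before surgery is 3 to 4 weeks (assumed), an intervention patient is called about 12 + 3 = 15 to 12 + 4 = 16 times. A control patient is called 0 times by this route.

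**Illustration of unequal detection.** It applies only if call-detected events are counted in a between-arm comparison. Every rate is assumed; only the 125 per arm comes from the section on sample size.

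- Observed rate = true rate × probability of detection.
- True rate 20% in both arms; detection 90% with calls: 0.20 × 0.90 = 18%.
- Chance of a false two-sided p < 0.05 = Φ{[d − 1.96·√(2·p̄(1 − p̄)/n)] / √[(p₁(1 − p₁) + p₂(1 − p₂))/n]}, where d = p₁ − p₂, p̄ is the mean of the two observed rates and n = 125.

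| Control detection | Control observed | Difference | Extra patients per 125 | Ratio | False p < 0.05 |
|---|---|---|---|---|---|
| 70% | 0.20 × 0.70 = 14% | 4 points | 0.04 × 125 = 5 | 18/14 = 1.29 | 14% |
| 50% | 0.20 × 0.50 = 10% | 8 points | 0.08 × 125 = 10 | 18/10 = 1.8 | 45% |
| 30% | 0.20 × 0.30 = 6% | 12 points | 0.12 × 125 = 15 | 18/6 = 3.0 | 84% |

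Worked for the middle row: p̄ = 0.14; [0.08 − 1.96 × √(2 × 0.14 × 0.86/125)] / √[(0.18 × 0.82 + 0.10 × 0.90)/125] = (0.08 − 0.0860)/0.0436 = −0.138, and Φ(−0.138) = 0.445.

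With a true rate of 10%, the three chances are about 8%, 24% and 52%. With 30%, they are about 20%, 65% and 96%. The ratios do not depend on the true rate; they restate the assumed detection gap. The table shows that a moderate gap would matter, not that one of this size exists.

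**The case against.** A reader might infer that falls, hernias and dizziness are recorded only in the calls, so that the safety conclusion has no comparator. The documents do not support that. The CTCAE register runs for the whole study without restriction by arm, the Background rests safety on adverse events in general, and complications, readmissions and deaths are recorded in both arms. The restriction to calls is true only of events labelled exercise-related.

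It can also be said that a tally of events caused by exercise is by definition mainly a description of the delivered programme. The section on statistical analysis plans no between-arm test of it, and nothing says that call-detected events enter the register. The data flow may be settled in the full protocol or in the schedule in Table 2, neither of which is visible. All of this stands, and it makes the harm conditional.

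It does not remove the asymmetry. The register has no stated elicitation interval, and the survey's stated subject leaves out falls and hernias. A minor home event in a control patient therefore has no described weekly route that matches the call.

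Two objections to possible remedies also stand. Removing call-detected events from the adverse event table would hide known harms. A checklist that mentions exercise could unblind the assessor before SPPB and Barthel are scored.

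**Conclusion.** The point holds in limited form. A comparator exists, but the listed event types are ascertained unequally: one arm is asked weekly by the unblinded deliverer, while the other relies on a register with no stated interval and on a survey about treatment toxicity. The bias runs against exercise if call-detected events feed the register. If they are kept apart, the exercise-related count is uncontrolled and its attribution is not independent.

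The size cannot be derived from the documents. The spread above (4 to 12 percentage points, or 5 to 15 extra patients per 125) rests wholly on an assumed 20% true rate and assumed detection probabilities. The conclusion also assumes that the calls go to the intervention arm only, as every description of them implies. This should be put right because safety is a stated aim, but it does not undermine the primary outcomes.

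**What to change.** - At the existing visits (discharge, 1, 3 and 6 months), ask both arms the same short checklist of the event types in the adverse event section. Word it neutrally and do not ask whether exercise was the cause. Ask it after the blinded outcome assessments are scored, or have medical staff ask it.
- Name that checklist as the source for the between-arm comparison of these event types.
- Keep every call-detected event in the safety report, flagged by source and listed descriptively for the intervention arm. Delete none. State whether such events also enter the CTCAE register.

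**Cost.** One page in the REDCap visit forms and a few protocol sentences; no new visit or staff. Recall at visits, over up to three months, will miss some minor events. The loss may not be equal, because intervention patients keep an exercise diary and have weekly calls that can prompt memory. A small risk of unblinding remains, which the order of questions limits.
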